### Sample size

The target sample size is 85 participants in each trial group. This is based on 90% power and a 0.05 two-sided statistical significance to detect a minimally clinically important difference of ten points on the SPADI total scale,^24^ using a conservative estimation of a baseline SD of 20.^25^ Accounting for a potential loss to follow-up at 12 months of 20%, this will require a total of 213 patients to be randomised to the intervention groups.

### Recruitment

All patients (≥18 years old) consulting their GP for shoulder pain who are suitable for both a local corticosteroid injection and physiotherapist-led exercise therapy can be invited by their GP to participate in this study. These patients will be informed on the trial by the GP and are advised to contact the research team. The research team will provide further information on the trial and if the patient confirms their interest to participate in the trial, eligibility will be checked and the informed consent procedure will be completed. After the participant has completed the baseline questionnaire, the patient will be randomised by the research team. The patient and the GP will be notified on the randomisation result by the research ream.

All other patients (eg, wait-and-see policy or prescription of analgesics) will be invited to participate in the parallel cohort study. These patients will be invited through two weekly searches of the medical records of participating GP practices. All cohort participants will be informed that if the initial GP treatment fails and they consider re-consultation, they are potentially eligible for the RCT (figure 1).

**Figure 1 F1:**
[figure not shown]
Consort flowchart of recruitment. GP, general practitioner.

Accounting for a 25% willingness of patients to participate in the RCT and in the cohort, a 50% willingness of participants in the cohort to enter the trial if initial treatment fails and a 25% loss due to not eligible for the trial, 2430 patients need to be invited to participate in either the trial or the cohort over the 18 months period. On average, a fulltime Dutch GP has around 2095 registered patients.^26^ With an incidence rate of 30.3 per 1000 person-years in the Netherlands,^3^ it is expected that a fulltime GP sees around six patients with a new episode of shoulder pain per month, which results in 23 GPs needed for this study. However, taking in account Lasagna’s law,^27^ we expect to need at least 46 GPs to ensure the total sample size.

### Allocation

The Erasmus MC Clinical Trial Center, who will not meet or contact the patients will prepare a remote web-based randomisation system using random blocks of 8, 6 or 4 to ensure concealment of allocation. Participants and their GP will be informed about the outcome of the randomisation by phone and participants will receive a patient card through mail detailing their treatment allocation and related procedures.

### Blinding

The researcher who will carry out the primary analysis will be blinded for treatment allocation. The participant and the GP will not be blinded for treatment allocation. This is not feasible in this pragmatic trial.

### Data collection methods

After obtaining informed consent, participants will complete the baseline questionnaire. Subsequently, the participants will be randomised to one of the two interventions groups. Participants will be asked to complete online questionnaires sent by email, after 6 weeks, 3, 6, 9 and 12 months after randomisation. If the follow-up questionnaire is not returned within 2 weeks of initial mailing, a reminder will be sent encouraging the participant to complete the questionnaire. Non-responders or responders with incomplete questionnaires will be contacted by telephone to pose them the missing questions.

### Data management

Data management will be performed via a web-based medical survey tracker (Gemstracker). Each participant will be allocated a unique code, which will be used on all trial-specific documents, except for the signed informed consent and contact details. Participants’ identifiable data will be stored separately and securely from study data in accordance with local procedures.

### Statistical methods

Baseline characteristics will be summarised using descriptive statistics. All analyses will be performed under intention-to-treat.

#### Primary analyses

The primary clinical outcome is patient reported severity of pain and function over 12 months post randomisation, measured with the SPADI total score. A linear mixed model with repeated measures will be used to generate estimates of effects. The time points included in this model will be baseline, 6 weeks, 3, 6, 9 and 12 months. Baseline values for the primary outcome are retained as part of the outcome vector and group means on the primary outcome are assumed to be equal at baseline (ie, an intervention-effect is restricted at baseline). Fixed effects will be time and time by treatment group. To model the covariance of repeated measures by participant, the option for data structure in the analyses will be set on ‘unstructured’ and the model which yields the lowest Akaike’s information criterion will be chosen. The following baseline measurements will be considered as covariates: age, gender, duration of pain, concomitant neck pain and history of shoulder pain.^28–30^

#### Secondary analyses

The cost effectiveness will be evaluated using the incremental cost per QALY gained of the corticosteroid injection versus physiotherapist-led exercise therapy, using both the healthcare as well as the societal perspective, using a time horizon of 12 months. Non-parametric bootstrapping will be used to depict the degree of uncertainty for costs and health effects and the cost-utility ratio in a cost-effectiveness plane. In addition, an acceptability curve will be drawn, which indicates the probability that the intervention studied has lower incremental costs per QALY gained than various thresholds for the maximum willingness to pay for an extra QALY. Similar methods will be used to estimate the cost effectiveness of both interventions in the short term (6 weeks and 3 months) and medium term (6 and 9 months).

In addition, secondary analyses include shoulder pain-intensity, shoulder function, global perceived effect, quality of life, sleep quality, work absence, healthcare utilisation and side effects and will be evaluated at all follow-up time points using linear model regression methods for numerical outcomes and logistic regression methods for dichotomous outcomes. The clinical effectiveness at all other follow-up time points will be estimated using similar methods described for the primary analyses.

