### Interventions

#### Corticosteroid injection

The corticosteroid injection will be delivered by the GP. The corticosteroid injection will consist of 40 mg triamcinolone acetonide (Kenacort-A 40), possibly in combination with a local anaesthetic agent, lidocaine 10 mg, at the discretion of the GP in accordance with the NHG guideline for shoulder pain.^8^

The site of the injection, subacromial or intra-articular, will depend on the initial diagnosis of the GP. Subacromial injections will be administered to participants diagnosed with subacromial pain syndrome and intra-articular injections on participants with glenohumeral joint pain. GPs are advised to follow the instructional videos on subacromial and intra-articular injection published by the NHG.^13^ All participating GPs will be invited for an optional shoulder injection training by an experienced doctor of orthopaedic medicine at the Erasmus MC.

Consultations with the GP will be coordinated so that participants typically receive their injection within 1 week of randomisation. In line with the guideline, a maximum of two injections will be permitted per patient, with the second injection, when considered necessary, offered 2–4 weeks after the first injection. Any participant receiving a second injection will have the date of administration recorded in their case report form.

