#### Physiotherapist-led exercise therapy

Participants randomised to physiotherapist-led exercise therapy will be referred to one of the local physiotherapists. Preferably the physiotherapist is affiliated with the Dutch Shoulder Network (SNN). The SNN is an umbrella organisation for regional shoulder networks of physiotherapist practices. All affiliated physiotherapists have to complete a 2-day entry course on shoulder pain, accredited by the Royal Dutch Society for Physiotherapy (KNGF).

The exercise therapy will consist of a maximum of 12 treatments of around 30 min under the supervision of the physiotherapist over a course of 12–14 weeks. In addition, all participants will receive home-based exercise at the discretion of the physiotherapist. The intensity of the exercise is based on tissue irritability and the capacity of the patient. Pain during or after exercise is allowed, as long as there is no night-time pain and the pain returns to pre-training levels within 24 hours. Physiotherapist will be requested not to use massage, laser therapy, ultrasound therapy, transcutaneous electrical nerve stimulation, dry needling or acupuncture, given lack of evidence for effectiveness.^14^ All participating physiotherapists will receive a brief guideline developed in cooperation with the SNN describing the criteria for exercise therapy.

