### Outcomes

Table 1 shows an overview of the time schedule of enrolment, interventions and all assessments for participants. The selection of outcome measures has been based on the core outcome set published by The Outcome Measures in Rheumatology (OMERACT) Shoulder Working Group.^16^ The primary outcome is shoulder pain-intensity and function measured using the Shoulder Pain and Disability Index (SPADI) total score over 12 months post randomisation.^17^ The SPADI is the most commonly used measure to assess pain-intensity and disability.^18^ The Dutch version of the SPADI has good psychometric properties.^19 20^

**Table 1 T1:** Time schedule for enrolment, interventions and assessments for participants

Time point	Pre- randomisation	Baseline (T0)	6 weeks (T1)	3 months (T2)	6–9–12 months (T3–T4–T5)*
Enrolment					
Diagnosis	X				
Eligibility screening	X				
Informed consent	X				
Randomisation†		X			
Interventions					
Corticosteroid injection†		X			
Physiotherapist-led exercise therapy†					
Assessments					
Sociodemographics		X			
Current shoulder episode (location, duration, cause, course, stiffness)		X			
Previous shoulder episodes (history, treatments)		X			
Other current pain locations (pain manikin)		X			
Other relevant medical issues		X			
Psychological prognostic factors (HADS, FABQ)		X			
Current medical use for the shoulder pain		X			
Treatment preferences		X			
Treatment expectations		X			
Outcomes					
Pain and function (SPADI)		X	X	X	X
Medical costs (MCQ)			X	X	X
Global perceived effect (GPE)			X	X	X
Productivity costs (PCQ)			X	X	X
Health-related quality of life (EQ-5D-5L)		X	X	X	X
Sleep quality (SQS)		X	X	X	X
Side effects			X	X	
Serious adverse events (SAEs)			X	X	X

*At these time points the indicated outcome measures will be repeated.

†Randomisation occurs after baseline measurements are taken.

EQ-5D-5L, five-level version of the well-validated EuroQol Five-Dimensional Questionnaire; FABQ, Fear-avoidance Beliefs Questionnaire; HADS, Hospital Anxiety and Depression Scale; MCQ, Medical Cost Questionnaire; PCQ, Productivity Cost Questionnaire; SPADI, Shoulder Pain and Disability Index; SQS, Sleep Quality Scale.

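### The acceptability curve is worded as a cost-per-QALY ratio below a threshold, a criterion that is valid only where injection gains QALYs

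*Protocol article*

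**What the plan says.** In the protocol article, Secondary analyses, the economic measure is the "incremental cost per QALY gained of the corticosteroid injection versus physiotherapist-led exercise therapy", from two perspectives and "using a time horizon of 12 months". On uncertainty it says: "Non-parametric bootstrapping will be used to depict the degree of uncertainty for costs and health effects and the cost-utility ratio in a cost-effectiveness plane". It then adds an acceptability curve, which is to indicate "the probability that the intervention studied has lower incremental costs per QALY gained than various thresholds" of willingness to pay for one more QALY. Similar methods are planned at 6 weeks and at 3, 6 and 9 months. Net monetary benefit is not mentioned, and no rule is given for replicates in which injection yields fewer QALYs.

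Two other places bear on where the replicates may fall. The injection arm is limited in that "a maximum of two injections will be permitted per patient" (Corticosteroid injection). The exercise arm consists of "a maximum of 12 treatments of around 30 min" (Physiotherapist-led exercise therapy). The Objectives section names cost effectiveness as the main secondary objective.

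**The concern.** A ratio discards the sign of its denominator. The same positive ratio can mean paying for health gained or saving money for health lost, and a low value is good in the first case and bad in the second. A negative ratio can mean that injection dominates or that it is dominated. A test of ratio against threshold cannot tell these apart.

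The affected replicates are realistic here. One or two injections against up to 12 supervised sessions makes injection plausibly cheaper. The Introduction reports a small short-term pain benefit of injection that is not seen at 3 to 6 months, and a guideline that finds too little evidence to prefer either option. A 12-month QALY difference near zero, or below it, cannot be ruled out. At a true difference of zero, about half of all replicates have a negative QALY difference.

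The Discussion expects the results to bear on guidelines and possibly on the reimbursement of physiotherapy. Two perspectives and five horizons give up to ten curves that would share the same criterion.

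**Working it through.** **Notation.** dC = cost difference and dQ = QALY difference, both injection minus exercise. L = threshold. The article states no figure for the curve, so there is none to reproduce.

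**Step 1, algebra (no assumed numbers).** Injection is cost-effective at L when L x dQ - dC > 0.
- If dQ > 0, dividing by dQ gives dC/dQ < L, which agrees with the article's wording.
- If dQ < 0, dividing by dQ reverses the sign and gives dC/dQ > L, the opposite of the wording.

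The literal test is therefore right for every replicate with dQ > 0 and wrong for every replicate with dQ < 0. With dC > 0 and dQ < 0 (dominated) the ratio is negative, hence below any L of zero or more, and is counted as cost-effective. With dC < 0 and dQ < 0 the ratio is the saving per QALY lost; the test accepts small savings and rejects large ones.

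**Step 2, size (every input is an assumption).** dC and dQ are taken as independent normal variables with mean dC = -300 euro (SE 150) and SE of dQ = 0.02. Net benefit B = L x dQ - dC has mean L x mean(dQ) - mean(dC) and SD = sqrt((L x 0.02)^2 + 150^2).
- Net-benefit test: P(B > 0).
- Literal test: P(dQ > 0 and B > 0) + P(dQ < 0 and B < 0), by the bivariate normal distribution.

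Worked case, mean dQ = -0.02, L = 20,000: mean B = -400 + 300 = -100; SD = sqrt(400^2 + 150^2) = 427.2; P(B > 0) = Phi(-0.234) = 0.41. The literal test gives 0.158 + 0.592 = 0.75. The share of replicates with dQ < 0 is Phi(1) = 0.84.

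| Mean dQ | L (euro) | Both > 0 | Both < 0 | Literal | Net benefit |
|---|---|---|---|---|---|
| +0.03 | 20,000 | 0.933 | 0.017 | 0.95 | 0.98 |
| +0.02 | 20,000 | 0.841 | 0.050 | 0.89 | 0.95 |
| 0 | 20,000 | 0.499 | 0.240 | 0.74 | 0.76 |
| -0.02 | 20,000 | 0.158 | 0.592 | 0.75 | 0.41 |
| 0 | 0 | 0.489 | 0.011 | 0.50 | 0.98 |
| 0 | 50,000 | 0.500 | 0.383 | 0.88 | 0.62 |

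The close agreement at dQ = 0 and L = 20,000 is a cancellation: half the replicates are misclassified, in opposite directions. At the same dQ, thresholds of 0 and 50,000 do not cancel.

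If injection were instead 300 euro dearer (SE 500) with dQ = -0.02 (SE 0.02) and L = 20,000: mean B = -400 - 300 = -700, SD = sqrt(400^2 + 500^2) = 640.3, net benefit 0.14, literal 0.84.

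**Step 3, other assumed inputs.** Saving 300 euro, SE of dQ 0.025, L = 20,000, 200,000 simulated draws, literal v net benefit:
- cost SE 90: 0.96 v 0.98 at dQ = +0.04; 0.79 v 0.42 at -0.02.
- cost SE 600, for a societal perspective: 0.81 v 0.82 at dQ = +0.02; 0.68 v 0.45 at -0.02.

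The pattern is the same: a small gap where injection gains QALYs, and a crossing of 50% where it loses them.

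**The case against.** The strongest reply is that the sentence describes what the curve shows and is not an algorithm. It is common shorthand, and an analyst may well code net benefit behind it. A reader might infer that the plan defines the curve as the share of replicates with a signed ratio below the threshold. The article does not say that, so actual misclassification is not shown. This stands.

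It can also be said that a cost per QALY gained has no meaning where QALYs are lost, so that the sentence is merely silent on those replicates. That does not rescue it: they are then either miscounted or left without a rule. The planned cost-effectiveness plane would make the quadrants visible, which limits the risk of a hidden error, but it does not correct the probabilities on the curve.

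A condensed article may leave computation to a fuller document. That answers a complaint of missing detail. Here, however, a criterion is stated, and the stated criterion is wrong for part of its range.

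Finally, a reader might infer that the cost-effectiveness conclusion will be reversed. The documents do not support this. The large gaps at 20,000 euro need injection to be worse on QALYs, and the article predicts neither direction. The limits on injections and sessions speak to cost, not to QALYs.

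**Conclusion.** The concern holds as a defect of wording with a real consequence if the wording is followed. The algebra needs no assumptions: the stated criterion fails for every replicate with a negative QALY difference. The effect on the curve rests entirely on assumed costs, QALY differences, standard errors, independence and thresholds. At 20,000 euro it is negligible to small when injection gains QALYs or the difference is zero (95% v 98%; 74% v 76%), and it can cross 50% when injection loses QALYs (75% v 41% at -0.02). A reversed conclusion is possible, not demonstrated. Severity is minor to moderate: cost effectiveness is the main secondary objective, the primary SPADI analysis is untouched, and the curve can be computed correctly from the same replicates at any time.

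**What to change.** Replace the description of the curve with: at each threshold L, the curve shows the proportion of bootstrap replicates in which L x (QALY difference) - (cost difference) is greater than zero. Apply it to both perspectives and all five horizons. The cost is one sentence and one line of code, with no new data.

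As a separate, optional improvement, adjust the QALY difference within each replicate for baseline EQ-5D-5L, which Table 1 already collects. With 213/2 = 106.5 per group and an assumed utility SD of 0.15 to 0.25, the chance baseline imbalance has SE = SD x sqrt(2/106.5) = 0.021 to 0.034, similar in size to the QALY differences assumed above. The article does not say that QALYs will be unadjusted, so this is a suggestion and not a correction.

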#### Co-interventions

This is a pragmatic clinical trial designed to evaluate the effectiveness of corticosteroid injections compared with physiotherapist-led exercise therapy for shoulder pain in real-life routine practice conditions. Therefore, participants will be instructed to continue their usual medication as discussed with their GP. Co-interventions after randomisation will be allowed and will be monitored through medical record review and questionnaires. This includes cross-over between interventions, which is estimated to occur in 20% of participants based on the number of patients receiving an injection and referral for exercise therapy in the ‘usual care’ treatment arm of a recent RCT.^15^

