Secondary outcomes include incremental costs per quality-adjusted life year (QALY) gained, using both the medical as well as the societal perspective, over 12 months post randomisation. Medical costs will be measured using the Medical Cost Questionnaire (MCQ) and societal costs will be measured using the Productivity Cost Questionnaire (PCQ).^21^ QALY will be measured using the five-level version of the well-validated EuroQol Five-Dimensional Questionnaire (EQ-5D-5L) score.^22^

Other secondary outcomes will be clinical effectiveness and cost effectiveness of the randomised treatments in the short term (6 weeks, 3 months) and medium term (6 months, 9 months). In addition, secondary outcomes will include subdomains (pain and function) of the SPADI, health-related quality of life (EQ-5D-5L), sleep quality measured with the Sleep Quality Scale,^23^ participant’s perceived recovery using the global perceived effect questionnaire,^16^ work absence as measured by the PCQ, healthcare utilisation as measured by the MCQ, side effects assessed at short term post randomisation and serious adverse events (SAEs) occurring post randomisation.

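### Side effects are to be analysed at all five follow-up times but are scheduled for collection at only two, so the 6-, 9- and 12-month analyses have no systematic data

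*Protocol article*

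**What the plan says.** Two places in the protocol article point to 12 months.

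- **Statistical methods, Secondary analyses.** Side effects stand last in a list of eight outcomes: "healthcare utilisation and side effects and will be evaluated at all follow-up time points". Data collection methods gives those times: questionnaires go out "after 6 weeks, 3, 6, 9 and 12 months after randomisation".
- **Discussion.** Adverse reactions are named among the secondary outcomes said to be measured at the same five times.

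Two places stop at 3 months.

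- **Outcomes, text.** The outcome is defined as "side effects assessed at short term post randomisation". The same paragraph shows what short term means: "in the short term (6 weeks, 3 months) and medium term (6 months, 9 months").
- **Outcomes, Table 1.** The row reads "Side effects X X". The marks stand under 6 weeks and 3 months, and the combined 6–9–12-month column is empty. The row for serious adverse events is marked in all three follow-up columns.

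The Harms section adds that possible adverse events are picked up from patient questionnaires, contact with the research team and GP reports. It gives no end date. GPs and physiotherapists are asked specifically to report serious events and suspected unexpected serious reactions.

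**The concern.** Side effects are a listed secondary outcome of a trial meant to inform guideline recommendations. As written, the plan commits to between-group analyses at 6, 9 and 12 months for which no questionnaire item is scheduled. Either those analyses are silently dropped, or a comparison resting on questions asked up to 3 months is read as covering 12.

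Treatment also does not stop at 3 months. Supervised exercise runs "over a course of 12–14 weeks", so some courses can end after the last side-effect question. Cross-over is allowed: "This includes cross-over between interventions, which is estimated to occur in 20% of participants". The Sensitivity analysis section treats cross-over as something that happens at any time in the study period. A participant who first receives the other treatment after 3 months is never asked on schedule about its non-serious effects.

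**Working it through.** **1. Planned against scheduled times**

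| Time | Analysis planned (Secondary analyses) | Side-effect item (Table 1) | Serious adverse events (Table 1) |
|---|---|---|---|
| 6 weeks | yes | yes | yes |
| 3 months | yes | yes | yes |
| 6 months | yes | no | yes |
| 9 months | yes | no | yes |
| 12 months | yes | no | yes |

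The item is scheduled at 2 of 5 times, so 3 of 5 analyses have no scheduled data. The other seven outcomes in the sentence come from instruments that Table 1 marks at every follow-up time. Side effects are the only one of the eight for which the sentence fails.

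**2. Where the last question falls**

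- Three months = 365.25/12 × 3/7 = 13.04 weeks.
- Twelve months = 365.25/7 = 52.18 weeks.
- Follow-up after the last side-effect question = 52.18 − 13.04 = 39.1 weeks, and 39.1/52.18 = 75%.

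**3. Allocated treatment against that date**

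- Injection: the first is typically within 1 week of randomisation, and a second may follow 2–4 weeks later (Corticosteroid injection section). The latest usual time is 1 + 4 = week 5, well before week 13.
- Exercise, started at week 0: ends at week 12–14. The part after the 3-month questionnaire is 0 to 14 − 13.04 = 0.96 weeks, or at most 0.96/14 = 7% of the course.
- Exercise, started at week 4: the article gives no start time, so this is an assumption. A 14-week course ends at week 18, and 18 − 13.04 = 4.96 weeks, or 35% of the course, falls after the questionnaire.

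**4. Cross-over**

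The plan's total reproduces: 2 × 85 = 170, and 170/(1 − 0.20) = 212.5, rounded up to 213. Expected cross-over is 0.20 × 213 = 42.6 participants. Co-interventions gives neither direction nor timing. The range below rests on two assumptions that are not in the article: 25–75% of cross-overs come after 3 months, and 30–70% of them go from exercise to injection.

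- Late exercise-to-injection: lowest 42.6 × 0.25 × 0.30 = 3.2; highest 42.6 × 0.75 × 0.70 = 22.4.
- Late injection-to-exercise: lowest 42.6 × 0.25 × (1 − 0.70) = 3.2; highest 42.6 × 0.75 × (1 − 0.30) = 22.4.

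The two ranges are identical. They illustrate how little the 20% figure fixes and are not an estimate of the number affected.

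**The case against.** The collection plan is consistent in itself: the Outcomes text and Table 1 agree on 6 weeks and 3 months, and short-term assessment looks deliberate. On this view the fault is loose grouping in one sentence, each outcome is meant to be analysed where it is collected, and a change of phrase is enough. That is a fair reading of how the slip arose, and correcting the text alone is a legitimate remedy. It does not remove the contradiction, because the Discussion repeats the 12-month schedule.

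A second objection is that capture does not cease at 3 months. Serious events are asked about to 12 months, and the Harms section names other routes without limiting them to serious events. This stands in part: late non-serious effects are not lost outright. But Table 1 puts no side-effect item in the later questionnaires, so what remains is unscheduled contact and reporting. That is a weak basis for the planned regression comparison between arms.

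A reader might also infer that the gap falls mainly on the exercise arm, because allocated injections end by about week 5 while exercise and cross-over injections come later. The documents do not support this. It counts cross-over as exposure in one arm and ignores it in the other, although late injection-to-exercise cross-over is equally unasked. Taking half of the 42.6 cross-overs (about 21) as late injections in the exercise arm would need both an even split and every such cross-over to come after 3 months; the article gives neither. The one difference it does show is the tail of the exercise course. With a prompt start that is at most about 1 week, and since reminders and telephone contact follow only after 2 weeks without a reply, some 3-month answers will arrive later than week 13.

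**Conclusion.** The contradiction is confirmed from the text alone and needs no assumption: three of five planned side-effect analyses lack scheduled data. The consequence is that the trial, as scheduled, can support a systematic comparison of non-serious side effects to 3 months and not to 12.

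Differential loss between arms remains possible but is not shown, and no patient count can be attached to it. Any such count rests on the direction and timing of cross-over, the start of exercise and a side-effect rate, none of which the article gives.

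This is a moderate point about a secondary outcome. It is worth acting on because it limits what can be concluded about harms and is cheap to correct.

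**What to change.** Reconcile the Secondary analyses section and the Discussion with the Outcomes text and Table 1.

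- **Preferred.** Add the existing side-effect item to the 6-, 9- and 12-month questionnaires, which are already sent and already carry the item on serious adverse events. Compare cumulative side effects to 12 months by randomised arm. Any summary by treatment received should be descriptive only: it is not a randomised comparison, and the plan states that all analyses follow intention to treat.
- **Otherwise.** Change the Secondary analyses and the Discussion to say that side effects are measured and analysed at 6 weeks and 3 months, and limit the conclusion on non-serious harms to 3 months.

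The first option costs a small amendment and a few extra items in three questionnaires. Participants already past those times will lack the item, and the report should say how many. The article describes recruitment as ongoing in November 2020, so the earlier the change, the fewer are affected. The second option costs only a correction of wording, but gives up a systematic comparison of non-serious effects over the last 75% of follow-up.
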